#### Sensitivity analysis

Two sensitivity analyses will be performed to assess the variation in the predictive performance of the eight COVID-19 prognostic models when implemented in different time periods: January 2021 to December 2021 and March 2020 to December 2021. Additionally, predictive performance in estimating the 90-day mortality risk will be evaluated in cohorts that have data available on this outcome (CliniCo, COVID-PREDICT, PHARMO, JHN/ANH/AHA, Ysis).

#### Sample size

Using national statistics from July 2020 to December 2021, the COVID-related mortality fraction for the older population (≥ 70 years) living at home in the Netherlands (including self-reported COVID-19-positive patients) was around 3% [3]. Although we expect higher mortality in nursing homes, hospitals, and ICU admissions, we will assume that an outcome incidence of 3% is the lowest event fraction that we will encounter for the current prediction model validation study. We take this fraction as a starting point for the sample size calculations, which are based on sample size calculation recommendations for external validation studies by Riley and colleagues [38]. Since we are considering various models, we base our sample size calculation around a general scenario that is reasonably applicable to all cases. Based on the distributions of predicted risk of mortality that were previously reported for some of the cohorts [8, 39], we assume the distribution of the linear predictor to be approximately N (− 3.9,1) [38]. Based on the calculations, a sample size of 754 will be required per cohort to validate an assumably well-calibrated model with a calibration-in-the-large coefficient of 0 and calibration slope of 1, and an assumed target standard error of calibration slope of 0.02. The target standard error of the calibration slope was chosen to ensure the evaluation of calibration with a higher precision than the typically used value of 0.05.

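### Under the protocol's own inputs, 754 participants per cohort give a calibration-slope standard error of about 0.23, not the stated 0.02

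*Protocol article*

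**What the plan says.** The protocol article, under Sample size, bases the calculation on published recommendations for external validation studies and prints its inputs:

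- **Event fraction:** "we will assume that an outcome incidence of 3% is the lowest event fraction that we will encounter".
- **Linear predictor:** approximately normal with mean −3.9 and variance 1.
- **True calibration:** "a calibration-in-the-large coefficient of 0 and calibration slope of 1".
- **Precision target:** "an assumed target standard error of calibration slope of 0.02".

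The result is that "a sample size of 754 will be required per cohort to validate an assumably well-calibrated model". The target is said to have been chosen "to ensure the evaluation of calibration with a higher precision than the typically used value of 0.05". No other precision criterion is offered for 754.

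Under Assessment of predictive performance, the calibration slope is a planned measure for the four models that are equations: GAL-COVID-19, NEWS2+, Xie and Wang. Table 2 shows that the GAL-COVID-19 model is validated in all six cohorts.

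**The concern.** At 3% mortality, 754 people yield about 23 deaths. A regression slope estimated from 23 events cannot have an SE of 0.02, so the sample size and the target do not look as if they belong together.

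This is the article's only sample-size justification, and it is applied to every cohort. If the SE were 0.02, an estimated slope of 0.6 would be decisive evidence of miscalibration. If the SE is about 0.23, the same estimate is compatible with a true slope of 1. A reader who accepts 754 as sufficient would therefore put too much weight on slopes from low-event cohorts, and on differences in slope between settings.

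**Working it through.** **Inputs (all from Sample size).** Linear predictor L ~ N(−3.9, 1); intercept a = 0; slope b = 1; n = 754; target SE(b) = 0.02; comparator SE 0.05.

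**Do the inputs agree with each other?** With p = 1/(1 + exp(−L)), the mean of p over N(−3.9, 1) is 0.0309. This matches the stated 3%, so the inputs are coherent. Expected deaths at n = 754 are 754 × 0.0309 ≈ 23.

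**Formula.** For the recalibration model logit(p) = a + bL, the information per person is

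- I_a = E[p(1−p)] = 0.02870
- I_ab = E[L·p(1−p)] = −0.08697
- I_b = E[L²·p(1−p)] = 0.28936

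and n × var(b) = I_a / (I_a·I_b − I_ab²).

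The denominator is 0.0083050 − 0.0075637 = 0.0007413, so n × var(b) = 0.02870 / 0.0007413 ≈ 38.72.

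**Attempt to reproduce the stated figure.**

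| Quantity | Calculation | Result |
|---|---|---|
| SE at n = 754 | √(38.717 / 754) | 0.227 |
| 95% interval around slope 1 | 1 ± 1.96 × 0.2266 | 0.56 to 1.44 |
| n for SE 0.02 | 38.717 / 0.0004 | about 96,793 (about 2,990 deaths) |
| n for SE 0.05 | 38.717 / 0.0025 | about 15,487 |

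The 754 is not reproduced. The SE ratio is 0.227 / 0.02 ≈ 11, and the ratio of sizes is 96,793 / 754 ≈ 128.

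**Simulation check.** Cohorts of 754 were simulated from the same inputs. The empirical SD of the fitted slope was 0.237 in one run of 4,000 cohorts and 0.241 in another of 1,000. Both agree with the formula.

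**Readings that might rescue 754.**

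- *0.02 misprinted for 0.2:* needs 38.717 / 0.04 ≈ 968, not 754. It would also contradict the statement that the target is tighter than 0.05.
- *Wider linear predictor, mean −3.9:* SD 1.5, 2 and 3 give SE 0.146, 0.115 and 0.095 at n = 754.
- *Intercept held fixed:* √(1 / (754 × 0.28936)) = 0.068.
- *Higher mortality:* assuming 30–50% risk and a linear-predictor SD of 0.7–1.3 (not figures from the protocol), SE at n = 754 is 0.08 to 0.13, and SE 0.02 needs about 13,300 to 32,000.
- *Any distribution at all:* var(b) is at least 1/(n·I_b). For a calibrated model I_b cannot exceed the maximum of x²p(1−p), which is 0.4392 at x = 2.40. So at n = 754, SE ≥ √(1 / (0.4392 × 754)) = 0.055, and SE 0.02 needs at least 1 / (0.4392 × 0.0004) ≈ 5,692.
- *Target entered as a variance of 0.05:* 38.717 / 0.05 ≈ 774, within 3% of 754, with SE about 0.22. This is the only near match found. It suggests a mix-up of variance and SE, but the document does not show the calculation, so it remains a conjecture.

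**The case against.** The strongest reply is that 754 is a required minimum and 3% is the lowest event fraction expected. Actual cohort sizes are not given, and the protocol expects higher mortality in hospitals and nursing homes, so achieved precision may be better than 0.23. That is correct, and it limits the finding to the printed calculation: nothing here shows what precision the study will achieve. It does not repair the claim, because the bound of 0.055 holds for 754 at any event fraction.

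A second reply is that the consequences are contained. The slope is planned for four of the eight models. It sits beside the c-statistic, calibration plots, calibration-in-the-large and decision curves. Each performance measure will be reported with a 95% confidence interval, so a wide interval would be visible. The planned update is to the intercept only, so no slope update depends on this SE. All of this stands, and it means the error does not invalidate the analyses. The published justification is still wrong as written, and it tells readers to expect intervals about one-eleventh as wide as its own inputs imply.

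It is also fair to say that the document does not reveal whether the size or the target was misreported.

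**Conclusion.** The concern holds. Given the protocol's own inputs, 754 participants per cohort deliver a calibration-slope SE of about 0.23, not 0.02, and the stated target would need about 96,800. No choice of risk distribution for a well-calibrated model brings 754 down to 0.02, or even to the 0.05 that the plan says it improves on.

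The 0.227 rests on the printed N(−3.9, 1), a true slope of 1 and the large-sample information formula, which simulation supports. The 0.055 bound needs only that the model is calibrated. The conclusion concerns the stated size and its stated precision; precision in the actual cohorts depends on sizes that the article does not give.

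**What to change.** Correct the Sample size section so that the size and the target agree:

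1. State that under N(−3.9, 1) and about 3% events, n = 754 gives SE(slope) of about 0.23 (95% half-width 1.96 × 0.2266 ≈ 0.44) and, with the slope fixed at 1, SE(calibration-in-the-large) of about 0.215.
2. Delete the sentence claiming better precision than 0.05.
3. If 0.02 is kept as an aim, state that it needs about 96,800 participants per cohort in the 3% scenario. If 754 came from another criterion, such as a variance, name that criterion and show the calculation.

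Giving the expected SE for each cohort from its actual size, event fraction and linear-predictor spread would help readers, but the correction does not depend on it.

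The cost is rewording and one recalculation. The cohorts already exist, so no patients are added. The stated precision becomes less favourable.

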## Discussion

This external validation study will assess the predictive performance of pre-existing clinical and COVID-19-specific prognostic models in the older population. Our study will reveal the validity of these COVID-19 prognostic models in one of the most vulnerable populations, the older population, as well as give insight into the requirements for tailored prediction models for the older population in future COVID-19 waves or pandemics.

While previous studies have largely focused on external validation of COVID-19 prediction models in the general adult population [14, 40, 41], this external validation study will focus on evaluating the performance of existing COVID-19 prognostic models specifically in the older population which represents the highest proportion of hospitalized COVID-19 patients and the highest mortality [3].

External validation in multiple cohorts across different healthcare settings allows for the assessment of between-setting heterogeneity in predictive performance and applicability at different points of care in older COVID-19 patients. This is one of the first studies to evaluate prognostic models for COVID-19 disease in individuals living in nursing homes.

### Challenges and limitations

There are certain challenges that we anticipate encountering while conducting this research. Definitions of participant inclusion and predictor measurement procedures are expected to differ across cohorts. Although we have carefully planned to collect information on the definition of a COVID-19 infection and predictor measurements for each cohort, we cannot rule out the possibility of heterogeneity occurring across different settings and its effects on model performance [42]. However, this heterogeneity resembles practical conditions encountered in clinical practice and thus provides relevant knowledge on the anticipated performance of the models in clinical practice.

A limitation of this study is that not all low risk of bias COVID-19 prognostic models identified by the living systematic review could be included in this external validation. This was due to the lack of predictor information available in the cohorts. Similarly, predictor measurements and incidence of mortality due to COVID-19 can vary over time due to newer variants, better medical management, and improved vaccination coverage [43]. These temporal changes can potentially limit the predictive performance of the prognostic models being investigated in the current study.

## Conclusion

External validation of newer and existing COVID-19 prognostic models can provide evidence about their predictive performance when implemented in the older population as tools of effective risk stratification and in aiding decision-making for targeted and timely clinical interventions.

## Data Availability

The datasets generated and/or analyzed during the current study are not publicly available due to confidentiality. COVID-OLD, CliniCo, COVID-PREDICT, PHARMO, and JHN/ANH/AHA are available on reasonable request.

## Abbreviations

PCR: Polymerase chain reaction
APACHE score: Acute Physiology and Chronic Health Evaluation score
NEWS score: National Early Warning Score
SOFA score: Sequential organ failure assessment score
PROBAST: Prediction model Risk of Bias Assessment Tool
RT-PCR: Reverse transcription polymerase chain reaction
JOMO: Joint modeling
LOESS: Locally estimated scatterplot smoothing
